### Research questions

RQ1. Is the INCLUSIVE intervention implemented over three school years more effective and cost-effective than standard practice in reducing bullying and aggression among 12- to 15-year olds in English secondary schools?

RQ2. Is the INCLUSIVE intervention more effective than standard practice in improving students’ quality of life (QoL), well-being, psychological function and attainments, and reducing school exclusion and truancy, substance use, sexual risk, National Health Service (NHS) use, police contacts among students, and improving staff QoL and attendance and reducing burn-out?

RQ3. What pre-hypothesised factors moderate and mediate the effectiveness of the INCLUSIVE intervention; including, do effects vary by socio-economic status and sex?

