### Randomisation

Eligible schools whose head-teacher gives informed written consent to participate will be allocated with a 1:1 ratio between intervention and control arms. Stratified randomisation will be undertaken remotely by the Clinical Trials Unit (CTU) at the London School of Hygiene & Tropical Medicine (LSHTM). To promote baseline equivalence, we will stratify by key school-level determinants of violence:Single sex versus mixed sex school.School-level deprivation, as measured by percentage of students eligible for free school meals (low/moderate 0 to 23%; high >23%, with 23% being the median for England).School ‘best eight value added’ in GCSE exams (above and below median for England of 1,000). Value added (VA) score is a school-level measure of students’ attainment in public exams adjusting for their attainment on entry to the school. We use VA rather than Ofsted ratings for schools as there is better evidence for VA being associated with violence rates [59].

Schools will be allocated randomly within each of these eight strata.

Protecting against selection bias:School level: the randomisation schedule will be drawn up once the schools have consented and after the baseline survey, thus guarding against selection biases at entry of clusters to the trial. The randomisation may occur sequentially in groups of 10 schools, should there be any delays with baseline surveys in some schools. As with most social intervention trials, schools, their students, teachers and other staff cannot be ‘blinded’ to allocation status. However, fieldwork staff will be blinded to allocation as will data-input staff. Analysis of follow-up quantitative data will be undertaken blind to allocation.

Retention of control schools will be maximised by ensuring regular senior liaison and provision of participation incentives (£500 per school).(2)Student level: we had very high student participation in our pilot study: 96% of eligible at baseline and 93% at follow-up. To minimise bias, we will use in-school, mail and telephone contacts to try to include all enrolled students absent at either baseline or follow-up questionnaires. Note we will not attempt to follow-up students who have left the school.A flow chart of recruitment and intervention and control treatment is shown in Figure 1.

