### Power and sample size

The average English school has approximately 190 students per year, although this varies across schools. A systematic review of school-based secondary preventive interventions to prevent violence [69] reported a pooled effect size of 0.41 on measures of aggressive behaviour. Effect sizes for aggressive behaviour from similar interventions approximate 0.3 to 0.4 SDs in males. Recent data from three large UK school cohorts [70] suggest that intra-cluster correlation coefficients (ICC) for aggression and bullying outcomes vary between 0.01 and 0.03

We propose to recruit sufficient participants to detect a difference between groups of 0.25 SD with 90% power and a 5% level of significance. This is considered to represent a moderate size of effect and in line with the effect sizes seen in the literature.

Conservatively, taking an ICC of 0.04 and 150 students per school, a trial involving 20 schools per arm will provide 90% power to identify an effect size of 0.25 SD with a 5% significance level. If two schools per arm (that is 10%) were to be lost to follow-up over the course of the trial, we would still have 80% power to detect an effect size of 0.25 SD.

The total student sample size will be approximately 6,000. As we will be surveying all young people in the relevant school year at each follow-up, this sample is likely to remain similar across the study.

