Secondary analyses will include staff outcomes and will be carried out according to the principle of ITT using the same approach to modelling as described for the student outcomes. Secondary analyses will also examine moderators and mediators. We will examine whether intervention effects are moderated by individual-level gender and socio-economic status measured using the Health Behaviours in School-aged Children (HBSC) Family Affluence Scale [74] and sex, as well as by school-level stratifying factors (single sex versus mixed sex school; school-level deprivation; value added strata); and facilitator, though these analyses may be underpowered. We will examine whether intervention effects are mediated by process and intermediate outcome measures. Other such analyses will be informed by hypotheses derived from analysis of qualitative data.

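### Two school-level moderators are tied to randomisation strata cut from numeric measures; continuous interactions would usually have more power, at almost no cost

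*Protocol article*

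**What the plan says.** The moderator analyses are described in the protocol article under Outcome analyses. After individual-level sex and socio-economic status, the text adds "as well as by school-level stratifying factors (single sex versus mixed sex school; school-level deprivation; value added strata") and facilitator, and warns that these analyses may lack power.

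The stratifying factors are defined under Randomisation. Deprivation is "School-level deprivation, as measured by percentage of students eligible for free school meals (low/moderate 0 to 23%; high >23"%). Value added is "School ‘best eight value added’ in GCSE exams (above and below median for England of 1,000"). Both cut points are described as medians for England. With single-sex versus mixed schools, the three factors make eight strata, so each has two levels. The stated purpose of stratifying is balance between the arms at baseline.

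The third research question asks about moderators and mediators, including "do effects vary by socio-economic status and sex". No interaction effect size, moderator power or school-level distribution of either measure is given.

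**The concern.** A percentage and a numeric score must be known for every school before it can be placed in a stratum, so the finer measures are already in hand. A cut that serves to balance the arms need not be the scale on which moderation is tested. On the two-level scale a school at 24% and one at 60% count as the same, while schools at 22% and 24% count as opposites. The article gives no reason to expect the effect to change at 23% or at 1,000. Its Background describes social gradients in bullying, and it mentions no cut for the individual-level family affluence measure.

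A school-level interaction rests on 40 schools however many students are surveyed, so information discarded at that level cannot be recovered from student numbers. At stake is the chance of detecting that the intervention works differently across more and less deprived schools, or across higher and lower value-added schools.

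**Working it through.** **Inputs from Power and sample size.** "Conservatively, taking an ICC of 0.04 and 150 students per school, a trial involving 20 schools per arm will provide 90% power". The target difference there is 0.25 SD, with alpha set at 5%. A two-sided test is assumed, since sidedness is not stated.

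**The plan's own figure.** Design effect = 1 + (150 − 1) × 0.04 = 6.96. Effective number per arm = 20 × 150 / 6.96 = 431. Power for 0.25 SD is 95.6% (normal) or 94.7% (t, 38 df), against the stated 90%. With 18 schools per arm it is 93.6% or 92.2%, against the stated 80%. The stated figures do not reproduce, but they err on the cautious side and nothing below depends on them. No power is stated for any moderator, so there is no moderator figure to reproduce.

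**Variance of a school mean** (outcome SD 1): 0.04 + 0.96/150 = 0.0464.

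**Continuous interaction.** Let the effect change by b SD of outcome per SD of the school measure. With 20 schools per arm, SE = √(0.0464/20 + 0.0464/20) = 0.0681, and the noncentrality is b/0.0681.

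**Two-level interaction.** For a normal measure cut at its median, the halves differ in mean by 2√(2/π) = 1.596 SD, so their effects differ by 1.596b. With 10 schools per cell, SE = √(4 × 0.0464/10) = 0.1362. The noncentrality is therefore √(2/π) = 0.798 times the continuous one, and the cut keeps 2/π = 64% of the information.

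**Power, noncentral t on 36 df, two-sided 5%:**

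| b | Noncentrality, continuous | Power, continuous | Noncentrality, two-level | Power, two-level | Loss (points) |
|---|---|---|---|---|---|
| 0.05 | 0.73 | 11.0% | 0.59 | 8.8% | 2.2 |
| 0.10 | 1.47 | 29.8% | 1.17 | 20.7% | 9.1 |
| 0.15 | 2.20 | 57.3% | 1.76 | 40.1% | 17.2 |
| 0.20 | 2.94 | 81.5% | 2.34 | 62.5% | 19.0 |
| 0.25 | 3.67 | 94.6% | 2.93 | 81.3% | 13.3 |

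**Range at a median split.** A difference in effect between halves of 0.125 SD (b about 0.08) costs 5.6 points (20.1% to 14.5%). One of 0.50 SD costs 4.8 (99.4% to 94.6%), because both tests are then near certain to detect it.

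**Uneven splits.** The cuts are national medians, so south-east schools may not divide evenly. For a normal measure the retained information is φ(c)²/(pq), where p and q are the proportions of schools on each side of the cut and c is the matching normal quantile. That gives 57.6% at 30:70 and 53.9% at 25:75. If the continuous test had 80% power, the loss would be 19.2 points at 50:50, 21.5 at 35:65, 23.4 at 30:70 and 26.2 at 25:75.

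**Simulation** of 40 schools, b from 0.10 to 0.25, 4,000 replicates per cell, loss in points:
- normal measure, median cut: 7.8 to 20.4
- normal measure, cut 0.5 SD above the mean: 9.2 to 25.3
- skewed (gamma) measure, median cut: 8.4 to 25.0
- uniform measure, median cut: 5.6 to 14.7

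**Step instead of slope.** If the effect jumps at the cut, the ranking reverses. For a jump of 0.25 SD the two-level test has 43.2% power against 28.3% for the continuous one. For a jump of 0.40 SD it is 82.1% against 56.8%.

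**The case against.** The strongest reply is that the coding is not settled here. The word strata is attached only to value added. Deprivation is listed without it and is defined elsewhere as a percentage, so calling these stratifying factors could name which variables are examined rather than how they are coded. The article also says that subgroup analyses will be specified in advance, and the analysis plan is not shown. This stands in part: for deprivation the two-level form is an inference, and a reader who took it as written for both factors would be going beyond the text. It does not dispose of the point, because for value added the scale is stated, not left open.

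Second, the cuts are external medians fixed before randomisation. They are not data-driven, and examining effects by pre-specified stratification factors is ordinary practice. That is true; the weakness is inefficiency, not bias.

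Third, a slope of 0.10 to 0.20 SD per SD is 40% to 80% of the whole 0.25 SD design effect, which is large. With a smaller slope both tests are weak, and a null result says little on either scale. That also stands.

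Fourth, the third research question names socio-economic status, which the article measures on individual students. Treating school deprivation as part of that question is an interpretation.

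**Conclusion.** The point holds as a modest one about efficiency. The plan names a two-level scale for value added and, on the natural reading, for deprivation, although both come from numeric measures already held. If the effect changes roughly linearly with the measure, the two-level test loses about 2 points of power at b = 0.05 and roughly 5 to 26 points for larger interactions, given ICC 0.04, 150 students per school and 20 schools per arm. Within that range the size depends on b, the evenness of the split and the shape of the distribution, none of which the article gives.

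A reader might infer that the plan carries a fixed power loss of known size. The documents do not support that: the loss is conditional on linearity, nearly vanishes for very small interactions and becomes a gain for a true step at the cut. Nor does the point touch the primary analyses, stratification of the randomisation or use of the strata as covariates.

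**What to change.** In the Outcome analyses text, and in the analysis plan that follows it, pre-specify arm-by-continuous-score interactions as the moderation tests for these two factors, using percentage eligible for free school meals and the best-eight value-added score. Report effects by stratum (at or below versus above 23%; above versus below 1,000) as a descriptive display and a check on linearity. Single-sex versus mixed stays binary.

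The cost is a change of wording, with no new data. The downside is an assumption of linearity, which the stratum display lets a reader judge. If the investigators do expect a threshold at either cut, they should state that hypothesis and its reason, and the two-level test would then be justified.

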#### Economic analyses

The primary economic evaluation will be a cost-consequence analysis. We will undertake a cost-utility analysis as a secondary analysis. These analyses will be linked and use of both is consistent with NICE methods guidance for evaluating public health interventions. We propose using a multi-level modelling approach with random intercepts to estimate the mean and standard errors for both cost and effects along with the covariance matrix. From these data mean incremental net benefit and confidence intervals will then be estimated. Missing data will be handled using multiple imputation.

#### Process evaluation analyses

Qualitative data will be entered into the data analysis package NVivo (QSR International (UK) Limited, [name], United Kingdom, [contact]) which will be used to manage and code data. Qualitative data from the process evaluation will be subjected to a thematic content analysis. Codes will be applied to transcripts, which identify key themes and how these inter-relate in order to develop an analytical framework. Each transcript will be coded to indicate the type of participant, school and date, allowing analytical themes to be explored in relation to different groups’ experiences and to compare processes across schools. Drawing on methods associated with ‘grounded theory’, we will make constant comparisons and examine deviant cases to refine our analysis. Analysis will explore implementation and receipt and contextual factors affecting these, as well as potential causal pathways in order to develop hypotheses to examine in secondary moderator and mediator analyses. Additionally, quantitative data from surveys and observations will be used in analyses of intervention fidelity and reach using simple descriptive statistics.

### Ethical issues

The study has been approved by the Institute of Education Research Ethics Committee (18/11/13 ref. FCL 566) and the University College London Research Ethics Committee (30/1/14, Project ID: 5248/001).

### Consent

Written consent will be obtained at school level (head-teacher) for random allocation and for intervention, and at the individual student, staff and intervention facilitator level for data collection. For students, written age-appropriate information sheets will be provided in class one to two weeks before the baseline survey, together with oral explanation by teachers. Written consent will be required from all participating young people, which will be collected immediately before conducting the baseline survey. Young people will also be asked to take home written information sheets for parents. Parents who do not wish their child to participate will be asked to notify this opt-out in writing using a prepared form.

### Confidentiality

All information collected during the trial will be kept confidential and adhere to the 1998 Data Protection Act.

### Risk, burdens and benefits

#### Benefits

If successful, the INCLUSIVE intervention will result in the following benefits:Reduction of bullying and aggression which will be of benefit to all participants, the whole school, local communities and society in general.Reduction in other health-risk outcomes (for example, substance use) and improvements in mental health, emotional well-being and QoL.Reduction in costs to society related to bullying and aggression. These include reductions in NHS costs (related to violence and mental health problems), and in social costs including costs within the justice system.Benefits to school staff through increased access to restorative training and an improved school environment, which may improve staff well-being and QoL.Benefits to students who participate in the intervention, through opportunities for learning and improved self-efficacy.

#### Risks

There are no anticipated risks to participants or to schools. However, as in all interventions, there may be unanticipated risks. Harms will be assessed through examination of outcomes at 24 and 36 months. An independent Data Monitoring Committee (DMC) will examine any potential harms at 24 months. If any major harms are detected, the DMC will inform the Trial Steering Committee (TSC) who will decide what action should be taken.

It is possible that our approach may be ineffective, and its introduction in trial schools may prevent the use of more effective techniques to reduce aggression. Although some educational interventions to raise awareness of risk behaviours during adolescence have been shown to increase participation in these behaviours, we believe this is extremely unlikely in the case of this study because as our approach is based upon what is shown to be effective in systematic reviews. Because of the above, we believe that risks are minimal and that benefits justify the risks.

### Study governance

#### Trial documentation

Relevant trial documentation will kept for a minimum of 15 years.

#### Trial registration and conduct

The trial is registered with http://www.controlled-trials.com (ISRCTN 10751359); note that the ISRCTN for the pilot study was 88527078. As the trial is not within clinical settings nor using clinical samples nor using a medicinal product, there is no requirement to comply with the ‘The Medicines for Human Use (Clinical Trials) Regulations 2004’. We will follow the UK MRC Guidelines on Good Clinical Practice in Clinical Trials. Note that the chief Investigators (CI) and the majority of the other investigators have been trained in Good Clinical Practice for clinical trials.

#### Sponsor

The UCL Institute of Child Health, the employer of one of the CIs, will act as the sponsor of this trial.

TSC: the trial will be overseen by a TSC, including an independent chair ([name], University of Glasgow), at least two other independent members, Patient and Public Involvement representatives including young people and teachers involved in our pilot study, and an investigator representative of each institution involved in the research. Observers from the PHR programme will be invited to all TSC meetings. The TSC will meet six-monthly throughout the trial.

#### *Data Monitoring Committee*(*DMC*)

A DMC will be established independent of the investigators and of the TSC, but reporting to the TSC and (via the TSC) to the sponsors and the HTA programme. This will consist of an independent chair, a senior statistician and at least one other senior academic independent of the investigators. This will meet approximately yearly during the study. The DMC will monitor data for quality and completeness. Data quality, follow-up and trial monitoring will be facilitated through the development of a trial-specific database, including validation, verification, monitoring and compliance reports and follow-up report functionalities. The DMC will examine the results of an interim analysis at 24 months to consider any potential harms.

## Discussion

The INCLUSIVE trial is part of a growing number of cluster randomised trials related to health but conducted within the education system in the UK. We have built upon evidence from US and Australian studies, modified the intervention to include restorative justice elements and shown feasibility and acceptability in a pilot study. This full trial of the INCLUSIVE intervention is a pragmatic ‘realist’ trial, evaluating not only the facilitated intervention (for the primary outcome) but also a further year of the intervention when continued by schools without external facilitation.

A number of elements of the trial will aid generalisability and scalability if shown to be effective. We have included a very wide range of participating schools, including all but schools whose current functioning we judge to be too low to be able to implement or benefit from the intervention. The intervention is flexible and can be tailored to each school’s needs and we have partnered with a number of school networks to facilitate future scalability.

Funding was obtained from both the health sector (through the National Institute of Health Research) and the education sector (the Education Endowment Fund). Each is funding separate teams to undertake the research (health sector) and the intervention (education sector).

The trial will be overseen by an independent TSC and DMC appointed by the main funders (NIHR)

## Trial status

At time of submission (2 June 2014) the trial has recruited all schools and is currently recruiting and surveying students for the baseline survey. Schools will be randomised after all baseline data are collected.

## Abbreviations

AAYP: Aban Aya Youth Project
BBSCQ: Beyond Blue School Climate Questionnaire
CHU: Child Health Utility
CHU-9D: Child Health Utility 9D
CI: chief investigators
CTU: Clinical Trials Unit
DMC: Data Monitoring Committee
EEF: Educational Endowment Fund
ESTYC: Edinburgh Study of Youth Transitions and Crime
FGD: focus group discussion
GBS: Gatehouse Bullying Scale
HBSC: Health Behaviours in School-aged Children
HTA: Health Technology Assessment
ICC: intra-correlation coefficients
ITT: intention-to-treat
LSHTM: London School of Hygiene & Tropical Medicine
MRC: Medical Research Council
NHS: National Health Service
NICE: National Institute for Health and Care Excellence
NIHR: National Institute of Health Research
PedsQL: Paediatric Quality of Life inventory
PHR: NIHR Public Health Research programme
PSHE: Personal, Social and Health Education
QALYs: Quality-Adjusted Life-Years
QoL: quality of life
RCT: randomised controlled trial
SDQ: Strengths and Difficulties Questionnaire
SF: Short Form
SLT: Senior Leadership Team
SMT: Senior Management Team
SRD: Self-Reported Delinquency
SWEMWBS: Short Warwick-Edinburgh Mental Well-Being Scale
TSC: Trial Steering Committee
VA: value added
YPDP: Young People’s Development Programme
